**METHODOLOGY**

**Study design and participants:**

A prospective, open label, randomized controlled trial will be conducted at the Jordan University Hospital (JUH) in cooperation with [name] [name] from the respiratory team at (JUH), the Jordan Hospital and others public hospitals. An ethical approval will be obtained from the institutional review boards of the JUH, the Jordan Hospital and the Ministry of Health before starting the study.

All eligible patients between 17 and 80 years old attending the respiratory outpatient or the inpatient respiratory clinic in the hospitals will be invited to join the study and asked to sign a consent form before their participation.

Inclusion criteria include patients with an established asthma or COPD diagnosis by a respiratory physician, who were started on inhaler/s (pressurized metered dose inhaler (pMDI), turbohaler, accuhaler, handihaler, and soft mist inhaler) for a minimum of one month and are expected (as prescribed) to continue using their inhalers for a minimum of three months. Immunocompromised patients, patients who have difficulty in communication due to special needs or very severe clinical presentation will be excluded from the study.

Participants will be randomized into two groups. Simple randomization will be adopted; odd number for the educational intervention and even number for control.

Later each group will be provided, by a clinical pharmacist, with a different inhaler technique educational intervention (Non-invasive). The control group patients will receive an in-person TTG education consisting of a brief counseling on the proper use of inhalers followed by assessment. This cycle of assessment and counseling will be repeated up to three times if necessary, until the patient demonstrated correct technique on all steps.

Patients in the intervention group will receive a video-based teach-to-goal intervention on the proper inhaler technique using videos provided by the originator company of each inhaler type. Patients will be asked to watch a video (3-5 minutes in length) followed by assessment. If the assessment reveals incorrect use of the inhaler, the participants will be prompted to watch the video again and repeat until mastery will be demonstrated. If needed, the correct answer will be provided following 3 incorrect attempts. Patients in this group will be provided the video as a multimedia file to access it whenever they need re-education regarding their inhaler technique.

Based on published data, around 40% of Jordanian patients demonstrated proper inhaler technique after 3 months they have been provided the “Show-and-Tell” intervention, which is very similar to the TTG intervention (9). Thus, in order to detect 80% increase in the number of patients with correct use of inhaler, and accounting for 20% dropouts during the study period a sample size of 72 participants is required in each group at 95% statistical power and 5% significance level (Clincal.com).

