**Objectives:**

The objectives of the present research proposal are:

- To assess inhaler techniques, level of asthma/COPD control, medication adherence, quality of life and asthma- and COPD-related knowledge among Jordanian patients with asthma or COPD.
- To evaluate and compare the effectiveness of two methods of patient education on mastering inhaler technique among Jordanian patients with asthma and COPD; the traditional in-person TTG education and the video-based TTG one. This will be done immediately after the intervention and three months later.
- Assess the impact of the two interventions at the level of asthma and COPD control, medication adherence and quality of life on Jordanian patients with asthma and COPD after 3 months of the intervention.
- To evaluate the impact of the video-based TTG patient education on asthmatic and COPD patients with low literacy in comparison to high literacy patients.

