**Baseline assessment and outcomes:**

At baseline, data regarding demographics, asthma/COPD history, medication use including adverse effects, hospital admissions, and previous systemic corticosteroid use.

Inhaler technique as well as the level of asthma/COPD control, adherence to medication and the patients’ quality of life will be assessed at baseline.

Initially, all participants will be asked to use their inhaler in front of the clinical pharmacist and the proper technique will be assessed by the aid of standardized device-specific inhaler technique checklists (AstraZeneca Pharmaceuticals, GlaxoSmithKline, Boehringer Ingelheim Pharmaceuticals) translated into Arabic. Each checklist includes 9-10 steps, eight of them considered essential for the medication to reach the site of action. A score of 8/10 will be thus considered and classified as correct inhaler technique for all of them.

All participants will be assessed for their level of asthma or COPD control through validated Arabic version of the Asthma Control Test )ACT( or COPD assessment test (CAT) before intervention (38, 39).

Medication adherence and quality of life will be assessed by the Arabic versions of the validated 8-items Morisky medication adherence scale (MMAS) of the St. George’s respiratory questionnaire respectively before and after intervention (2, 40-42).

The primary outcome for this research project is to improve inhaler technique in patients with asthma and COPD. Secondary outcomes include increase the level of asthma and COPD control, improve medication adherence, and quality of life.

After collection of all information and assessment of parameters at baseline, patients will receive either the in-person education or the video-based teach-to-goal intervention. Participants will be then asked to use their inhaler as prescribed by the physician.

All patients will be followed up for 3 months, after which inhaler technique, level of asthma/ COPD control, adherence to medication and the patients’ quality of life will be assessed.

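### Unstratified allocation and unadjusted tests across two care settings and two diseases give up some precision, mainly on secondary outcomes; stratifying and adjusting would be a cheap improvement

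*Protocol*

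**What the plan says.** **Population.** In the protocol, Study design and participants, eligible patients "attending the respiratory outpatient or the inpatient respiratory clinic in the hospitals will be invited to join the study". The inclusion criteria take "patients with an established asthma or COPD diagnosis by a respiratory physician". Among other exclusions, patients with "very severe clinical presentation will be excluded from the study".

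**Allocation.** The trial is described as "A prospective, open label, randomized controlled trial". The same section fixes the method: "Simple randomization will be adopted; odd number for the educational intervention and even number for control". It mentions no blocking, stratification or minimisation. The size is given as "a sample size of 72 participants is required in each group at 95% statistical power and 5% significance level", so 144 in all.

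**Outcomes.** The third objective is to "Assess the impact of the two interventions at the level of asthma and COPD control, medication adherence and quality of life", three months after the intervention. Under Baseline assessment and outcomes, inhaler technique is primary; control, adherence and quality of life are secondary. All four are assessed at baseline and at three months. Control is measured by "Asthma Control Test )ACT( or COPD assessment test (CAT) before intervention", one instrument per disease. Quality of life uses the St. George's questionnaire in everyone.

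**Analysis.** The Analysis section compares the arms by t-test or Mann-Whitney test, and by chi-square or Fisher's test. It has no term for setting, diagnosis or baseline value. The SAP is not at hand.

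**The concern.** A patient enrolled as an inpatient may start from a worse point than a clinic outpatient and improve more over three months whatever education is given. Setting is then a prognostic factor for change in ACT, CAT and St. George's scores. Under simple randomisation its share can differ between the arms by chance, and with unadjusted tests its variation stays in the error term.

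Diagnosis matters for a different reason. ACT and CAT are separate scales, so control has to be compared within asthma and within COPD. The third objective therefore rests on two comparisons, each smaller than 72 per group, and the allocation does not control the split between arms within either disease.

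At stake is how precisely, and how convincingly, the trial can report on control and quality of life.

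**Working it through.** **1. The plan's sample size.** Protocol inputs: control rate 0.40, an 80% increase (read as relative, 0.40 × 1.8 = 0.72), two-sided 5%, power 95%, dropout 20%. With mean proportion 0.56:

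n = [1.960·√(2·0.56·0.44) + 1.645·√(0.40·0.60 + 0.72·0.28)]² / 0.32² = (1.376 + 1.093)² / 0.1024 ≈ 59.5, so 60 per group.

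Then 60 × 1.2 = 72, the plan's figure. It is sized on inhaler technique, not on control or quality of life. N = 144 is used below.

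**2. Chance imbalance in setting.** The protocol gives no inpatient share p, so a range is assumed. The SD of the difference in share between arms is about √[p(1−p)·4/144]. Simulating 200,000 simple randomisations of 144 patients gave:

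| Assumed inpatients | SD, formula | SD, simulated | P(difference ≥ 10 points) | P(difference ≥ 15 points) |
|---|---|---|---|---|
| 10% | 0.050 | 0.050 | 0.04 | 0.002 |
| 20% | 0.067 | 0.067 | 0.14 | 0.03 |
| 30% | 0.076 | 0.077 | 0.20 | 0.05 |
| 50% | 0.083 | 0.084 | 0.22 | 0.08 |

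**3. Effect on the estimate.** Assume inpatients recover 1 SD more than outpatients, where 1 SD is the within-setting SD of change. A 15-point imbalance then shifts that trial's arm difference by 0.15 × 1 = 0.15 SD. The shift is equally likely in either direction, so its average over randomisations is zero.

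**4. Type I error of the unadjusted t-test.** Simulation used 8,000 trials per scenario, with 20, 30 or 50% inpatients and 0.5, 1 or 1.5 SD extra recovery. The overall rate was 5.2 to 5.5%, essentially nominal. Among only those trials with an imbalance of 15 points or more, it was about 6–8%, 11–14% and 19–23% for the three sizes of recovery. These conditional rates rest on few trials (at 20% inpatients about 0.024 × 8,000 = 192) and are rough.

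**5. Precision.** With p = 0.30 and 1 SD extra recovery, the variance per patient is 1 + 0.30 × 0.70 = 1.21.

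- Setting left in the error: 2·√1.21/√144 = 0.183 SD with equal arms, and 0.185 in simulation with the arm sizes also random.
- Setting removed: 2/√144 = 0.167 SD.

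The reduction is about 10% (0.167/0.185 = 0.90).

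**6. Split within a disease.** Assume one third have COPD (48 patients). A split of 18:30 or worse has probability 2·P(X ≤ 18 | 48, 0.5) = 0.11. The cost is small: √(1/18 + 1/30) = 0.298 against √(1/24 + 1/24) = 0.289, about 3% in the standard error.

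**The case against.** **Chance imbalance is not bias.** This stands. Under genuine simple randomisation the expected error is zero and the 5% test already allows for imbalance (step 4). A reader might infer that natural recovery will be mistaken for a treatment effect. The raised error rates appear only after selecting badly imbalanced trials and assuming a large recovery, so the documents do not support that reading.

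**Nothing says the inpatients are acutely ill.** This also stands. The protocol says inpatient, and its Introduction speaks of access after discharge, which makes admissions plausible. It never says that these patients are exacerbating, and it excludes very severe presentations. Setting as a prognostic factor is a reasonable supposition, not a stated fact.

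**The disease split hardly matters.** Largely right. No text says ACT and CAT will be pooled, and within a disease the diagnosis cannot confound. What remains is the 3% in step 6.

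**Adjustment may be in the SAP.** Possible, and it would recover most of the precision. With 30% inpatients and a 15-point imbalance, the correlation of arm with setting is 0.15 × 0.5/√0.21 = 0.164, so the adjusted standard error is 0.167/√(1 − 0.164²) = 0.169. But the allocation method is fixed in the protocol, and no later analysis can restore balance.

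**Two neighbouring readings.** If odd and even refer to order of enrolment, allocation would be predictable; the protocol does not say where the numbers come from. Its before-after tests within each arm could credit recovery to education even with balanced arms. Both are separate questions, and stratification settles neither.

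**Conclusion.** The point holds as a cheap improvement, mainly for secondary outcomes. The protocol mixes two settings and two diseases, allocates without stratification and names only unadjusted comparisons between the arms. The trial remains valid: overall type I error stays near 5%, and the primary outcome, inhaler technique, is not obviously subject to spontaneous recovery.

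What is lost is about a tenth of the standard error on control or quality-of-life scores if 30% are inpatients and recover 1 SD more. There is also some credibility if the arms turn out visibly different. A difference of 10 points or more in inpatient share has probability from 0.04 (10% inpatients) to 0.22 (50%). Inpatient share, disease mix and extra recovery are all assumptions. With few inpatients or little extra recovery the loss is smaller still.

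**What to change.** **Allocation.** Replace the odd/even rule with a computer-generated, centrally held list in permuted blocks of varying size, stratified by setting at enrolment (inpatient or outpatient) and diagnosis (asthma or COPD). That makes four strata, both factors being known at enrolment. The list should be central, because lists held at each hospital would multiply the strata and leave many blocks incomplete.

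**Analysis.** Compare the arms at month 3 as follows:

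- ACT within asthma and CAT within COPD, each adjusted for setting and the baseline score.
- Technique, adherence and quality of life in all patients, adjusted for setting, diagnosis and the baseline value.

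The adjustment is needed with the stratification, since an unadjusted test after stratified allocation leaves setting in its error term and does not show the gain.

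**Cost.** No extra patients, visits or measurements. The downside is slightly more randomisation administration across the hospitals. The allocation change has to be made before enrolment; the analysis terms can go in the protocol or the SAP.

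### The odd/even allocation rule states no source for the number, no concealment and no time of reveal, which leaves assignment in an open-label trial open to foreknowledge or redrawing

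*Protocol*

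**What the plan says.** Under Study design and participants the protocol describes its design as follows: "A prospective, open label, randomized controlled trial will be conducted". On assignment it says "Participants will be randomized into two groups" and then gives the only procedure in the document: "Simple randomization will be adopted; odd number for the educational intervention and even number for control".

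The same section limits entry by a criterion that has no measurable threshold: "patients who have difficulty in communication due to special needs or very severe clinical presentation will be excluded from the study". It also says that all eligible attenders will be invited and will sign consent before taking part.

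A clinical pharmacist teaches both arms: "Later each group will be provided, by a clinical pharmacist, with a different inhaler technique educational intervention (Non-invasive". Under Baseline assessment and outcomes, technique is scored at entry when "all participants will be asked to use their inhaler in front of the clinical pharmacist". That section places teaching after the baseline data are collected. It does not place the reveal of the arm.

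The protocol nowhere names a sequence generator, a list holder, envelopes or a central allocation service.

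**The concern.** An odd/even rule tells anyone who knows the number which arm it means. Whether the assignment is protected then depends on where the number comes from and who can see it before the patient is committed to the trial. The protocol settles neither.

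This matters more here than in a blinded trial, because an open-label design has no later safeguard. The judgement-based exclusion gives foreknowledge a route into enrolment. Whether a patient communicates too poorly or is too ill to take part is plausibly related to how well that patient learns inhaler technique, which is the primary outcome. If such judgements were made with the next arm known, the arms could differ before any teaching took place. Intention to treat would not help, because the selection happens before entry. Adjustment reaches only traits that were measured.

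How patients are assigned and how the assignment is concealed is trial conduct, which the protocol has to fix. It is not a detail that a separate statistical analysis plan would normally supply.

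**Working it through.** **1. The plan's own figure.** The sample-size paragraph under Methodology gives a 40% control rate, an 80% increase (read as relative, so 0.40 × 1.80 = 0.72), 95% power, 5% significance and 20% dropout. The Analysis section makes tests two-sided. With unpooled variance:

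n = (1.960 + 1.645)² × (0.40 × 0.60 + 0.72 × 0.28) / (0.72 − 0.40)² = 12.995 × 0.4416 / 0.1024 = 56.04, so 57 evaluable per arm.

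57 / 0.80 = 71.25, so 72 per arm. The stated figure reproduces, and nothing in this point changes it. (The pooled-variance formula gives 60, and 60 × 1.20 = 72 as well. I use 57 below.)

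**2. The two readings of the number.**

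| | Enrolment or file number | Random digit |
|---|---|---|
| Is the sequence random? | No; with consecutive numbers it is alternation | Yes |
| Chance of knowing the next arm beforehand | 1.0 with consecutive numbers | 0.5 if concealed; up to 1.0 if the digit is drawn or seen first |
| Stated step against seeing or redrawing | None | None |
| Does the label simple randomisation fit? | No | Yes |

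The text does not decide between the columns. The third row is the same in both.

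**3. Timing.** Study design and participants puts randomisation before teaching. Baseline assessment and outcomes puts baseline measurement before teaching. Neither says whether the arm is known before or after consent, the eligibility decision and baseline scoring.

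**4. What selection could do (illustration).** Suppose there is no true effect. One arm has an expected three-month success rate of p₁ = 0.40, and selection alone lifts the other to p₂. The shifts are my assumptions; the documents give none. With n = 57 per arm and p̄ the mean of the two rates, the normal approximation to the chance of significance in the favoured direction is

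Φ{[(p₂ − p₁) − 1.96 √(2p̄(1 − p̄)/n)] / √([p₁(1 − p₁) + p₂(1 − p₂)]/n)}.

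For p₂ = 0.50: p̄ = 0.45, the null standard error is √(2 × 0.45 × 0.55/57) = 0.0932, and the other is √((0.24 + 0.25)/57) = 0.0927. This gives Φ[(0.10 − 0.1827)/0.0927] = Φ(−0.89) ≈ 0.186.

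Summing exact binomial probabilities over all outcomes that the two-sided chi-square test rejects gives:

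| Assumed shift | Rates | Two-sided rejection |
|---|---|---|
| 0 points | 40% v 40% | 0.048 |
| 5 points | 40% v 45% | 0.081 |
| 10 points | 40% v 50% | 0.184 |
| 15 points | 40% v 55% | 0.358 |

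**The case against.** The strongest reply is that the protocol says simple randomisation, whose ordinary meaning is a random number, and a random number read as odd or even is a valid generator. On that view the sentence is terse but not wrong. The protocol also intends to invite every eligible attender, which limits selective invitation, and it never says that allocation is open to those who recruit.

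Much of this stands. A reader might infer that the trial uses alternation, or that allocation is known to be unconcealed. The text supports neither as fact: alternation is one reading, and the absence of concealment is inferred from an open rule with no protective step beside it. A reader might also infer that the pharmacist will steer patients. No section says that the pharmacist recruits, screens or holds the sequence; the stated roles are teaching and assessing technique.

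The reply does not close the gap. Inviting all eligible patients is not a concealment mechanism, and eligibility itself turns partly on judgement. Even on the favourable reading, no stated step stops the person enrolling from seeing or redrawing the digit.

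Two further complaints are tempting and should not be made. Unequal arms are not a defect. A fair coin gives exactly 72/72 in 144 patients only 6.6% of the time, but power by the unpooled formula, after 20% dropout, is about 95.5% at 72/72 and still about 95.2% at 66/78. Lack of stratification by diagnosis or hospital is not an error either: chance imbalance under valid randomisation does not bias the test, and stratifying 144 patients by diagnosis and several hospitals could leave small strata.

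**Conclusion.** The point holds as a defect in how allocation is specified. Followed as written, the rule leaves assignment foreseeable on one reading and open to being seen or redrawn on the other, in an open-label trial with a judgement-based exclusion. It should be corrected before enrolment, because selection at entry cannot be reliably undone afterwards.

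Confidence is high that source, concealment and time of reveal are missing. It is not high that the numbers are enrolment numbers.

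The false-positive rates of about 8%, 18% and 36% depend entirely on the assumed shifts of 5, 10 and 15 points, with a 40% rate in one arm and 57 evaluable patients in each. They show how sensitive the test would be to selection; they do not estimate how much selection will occur. A reader might conclude that every between-arm comparison is already invalid. That would follow only if enrolment were in fact steered, which the protocol neither says nor implies.

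**What to change.** Replace the odd/even sentence under Study design and participants with text to this effect:

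- Participants are allocated 1:1 by a computer-generated random sequence prepared by a person who takes no part in recruitment.
- The sequence is concealed from recruiting staff by central allocation or by sequentially numbered, opaque, sealed envelopes.
- The arm is revealed only after consent is signed, eligibility is confirmed and all assessments listed under Baseline assessment and outcomes are complete.

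If the numbers are in fact enrolment or file numbers, that method should be abandoned, not just relabelled.

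The cost is a generated list, envelopes or an allocation service, and a short wording change. No extra patients or visits are needed, and the 72 per arm stays as it is. Blocking, stratification and terms for strata in the analysis model are optional and not needed to cure this defect.

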**Baseline assessment and outcomes:**

At baseline, data regarding demographics, asthma/COPD history, medication use including adverse effects, hospital admissions, and previous systemic corticosteroid use.

Inhaler technique as well as the level of asthma/COPD control, adherence to medication and the patients’ quality of life will be assessed at baseline.

Initially, all participants will be asked to use their inhaler in front of the clinical pharmacist and the proper technique will be assessed by the aid of standardized device-specific inhaler technique checklists (AstraZeneca Pharmaceuticals, GlaxoSmithKline, Boehringer Ingelheim Pharmaceuticals) translated into Arabic. Each checklist includes 9-10 steps, eight of them considered essential for the medication to reach the site of action. A score of 8/10 will be thus considered and classified as correct inhaler technique for all of them.

All participants will be assessed for their level of asthma or COPD control through validated Arabic version of the Asthma Control Test )ACT( or COPD assessment test (CAT) before intervention (38, 39).

Medication adherence and quality of life will be assessed by the Arabic versions of the validated 8-items Morisky medication adherence scale (MMAS) of the St. George’s respiratory questionnaire respectively before and after intervention (2, 40-42).

The primary outcome for this research project is to improve inhaler technique in patients with asthma and COPD. Secondary outcomes include increase the level of asthma and COPD control, improve medication adherence, and quality of life.

After collection of all information and assessment of parameters at baseline, patients will receive either the in-person education or the video-based teach-to-goal intervention. Participants will be then asked to use their inhaler as prescribed by the physician.

All patients will be followed up for 3 months, after which inhaler technique, level of asthma/ COPD control, adherence to medication and the patients’ quality of life will be assessed.

